**Fig. 1 Fig1:**
[figure not shown]
Flowchart of strength project

#### Specific aim 1

To study the effect of the multimodal intervention on cognitive performances, functional status, and mobility in MCI subjects by objectively measured parameters (baseline vs. follow-up 1, follow-up 2 and follow-up 3). Mobility (i.e., the ability of a subject to move in his/her environment) is often compromised in elderly people as a consequence of falls and other injuries and this could cause disability and reduced social engagement. The identification of approaches that might prevent motor–cognitive impairment would be a pivotal advancement in the correct management of aging people. Mobility will be evaluated by means of balance, walking test and gait speed; motor–cognitive function, defined as a process of coordination of movements finalized to a particular motor goal, will be measured by means of visual–spatial memory task.

The longitudinal monitoring of cognitive decline and dementia onset will also be implemented (follow-up 2 and follow-up 3).

#### Specific aim 2

To study the effect of the intervention on psycho-social aspects (e.g., psychological well-being, perceived stress, quality of life, metacognition and mood status), lifestyle characteristics and social network (baseline vs. follow-up 1, follow-up 2 and follow-up 3).

#### Specific aim 3

To study the effect of the intervention on specific biomarkers (baseline vs. follow-up 1, follow-up 2 and follow-up 3).

#### Experimental design aim 1

Neuropsychological as well as cognitive and clinical assessment, including cardiovascular, anthropometric, and functional evaluation (e.g., blood pressure, body mass index, ultrasound heart examination through standard echocardiogram, 6-min walk test, gait speed, Berg Balance Scale, handgrip strength, Physical Activity Scale for the Elderly, basic activities of daily living and instrumental activities of daily living) will be carried out (Table 1).

**Table 1 Tab1:** Clinical, functional, and neuropsychological assessment

Instruments
*Cognitive assessment*
Clinical Dementia Rating Scale—CDR [20]
Memory Complaint Questionnaire—MAC-Q [21]
Montreal cognitive assessment—MoCA [22]
Mini mental state examination—MMSE [23]
Rey auditory verbal learning test—RAVLT [24]
Phonological verbal fluency—PVF [24]
Supra-span of Corsi [25]
Semantic verbal fluency—SVF [26]
Attentive matrices [26]
Trail making test A−B—TMT A–B [27]
*Psychological assessment*

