### Randomisation

The selected subjects will be randomly allocated to the experimental group (EG, *n* = 150) or to the control group (CG, *n* = 150) using a randomisation list.

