### Sample size calculation

It was based on the null hypothesis that proportion of “success” and “failure” of the intervention is equal in the two groups (i.e., EG and CG), such as OR = 1.

Success and failure were defined on the basis of significant variation in the primary outcomes. Considering an OR = 1.5 indicative of an effect of the intervention, a total sample of 300 subjects allows us to reach a 90% of statistical power using logistic regression at the 5% level (two tailed). Drop-out rate was set at 20%.

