### Statistical analysis

All data will be collected in a database. A descriptive analysis will be performed to assess the distribution of variables and the presence of possible outliers. The latter will be checked and identified separately and then excluded from the analysis. For normally distributed variables, the comparisons between EG and CG at baseline will be carried out by *t *Student test or Chi-square test, while those between baseline and follow-up phases by paired sample *t* test. For non-normally distributed variables, non-parametric tests will be used. Correlation analysis will be performed to evaluate the relationships among variables and general linear models and repeated measures ANOVA will be used to assess the intervention effects adjusted for confounding variables (e.g., gender, age classes, marital status, schooling, drugs, and other variables that will emerge after analysis of secondary outcomes). The SPSS software will be employed.

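### Aims 1 to 3 and the paired t tests state the intervention effect as within-group change; for the continuous secondary outcomes, no EG versus CG contrast is named as deciding

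*Protocol article*

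**What the plan says.** The trial is randomised with a control group; subjects are "randomly allocated to the experimental group (EG, *n* = 150) or to the control group (CG, *n* = 150"). The three specific aims in the protocol article each ask for the effect of the intervention and then give a comparison in brackets:

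- Aim 1 (cognition, function, mobility): "by objectively measured parameters (baseline vs. follow-up 1, follow-up 2 and follow-up 3").
- Aim 2 (psycho-social aspects, lifestyle, social network): "lifestyle characteristics and social network (baseline vs. follow-up 1, follow-up 2 and follow-up 3").
- Aim 3 (biomarkers): "To study the effect of the intervention on specific biomarkers (baseline vs. follow-up 1, follow-up 2 and follow-up 3").

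None of the three mentions CG.

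The Statistical analysis section has two relevant sentences. The first, for normally distributed variables, says "the comparisons between EG and CG at baseline will be carried out by" a t or chi-square test, "while those between baseline and follow-up phases by paired sample *t* test"; non-parametric tests replace these where normality fails. The second says that "general linear models and repeated measures ANOVA will be used to assess the intervention effects adjusted for confounding variables". The examples of confounders are gender, age classes, marital status, schooling and drugs, plus others to be found when the secondary outcomes are analysed.

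**The concern.** The contrast written into the aims is the one that the analysis section gives to the paired t test. That test's null hypothesis is no mean change over time within a group. The question of a randomised trial is whether EG and CG differ. The two hypotheses part company whenever both arms change together, and three features make that plausible here:

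- The cognitive tests and questionnaires are repeated at baseline and three follow-ups, so retest gain is possible.
- Both arms receive psycho-education and the same clinical monitoring.
- Laboratory values may drift, and people with MCI may decline, up to the 2-year follow-up.

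The error can go either way. A gain or drift common to both arms gives a significant paired test in EG with no intervention effect. Conversely, the Discussion hopes for maintained gait speed and balance and slower conversion to dementia. If EG holds steady while CG declines, a paired test in EG finds nothing. The only simple EG versus CG test is at baseline, where randomisation already makes the null hypothesis true, so it carries no information on effect.

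**Working it through.** The plan states no figure for this point. The sample size section concerns the binary primary outcome; it supplies only the arm sizes, the two-sided 5% level and the drop-out rate.

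**What each named method tests**

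| Method in the plan | Null hypothesis | Answers an aim? |
|---|---|---|
| t or chi-square, EG vs CG at baseline | arms equal before treatment | no |
| paired t, baseline vs follow-up | no mean change within the group tested | no |
| general linear model / repeated measures ANOVA | depends on the term read: time, group, or group by visit | only through a between-arm term, which is not named |

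The time effect in a repeated measures ANOVA has the same defect as the paired test. If baseline is one of the repeated measures, the group main effect is diluted by a visit at which no difference is expected. The group-by-visit contrast is the one that answers the aim.

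**Inputs for the illustration**

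- From the document: n = 150 per arm, or 150 × 0.8 = 120 after 20% drop-out; two-sided 5%.
- Assumed, because the document gives none: the size of change, in units of the SD of change; independent subjects; the paired test run in EG.

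**Formulas** (normal approximation, upper tail; Φ is the standard normal distribution function)

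- Paired test in EG with mean change d: Φ(d√n − 1.96).
- Between-arm test of change with arm difference δ: Φ(δ√(n/2) − 1.96). If δ = 0 it rejects in 5%.

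**Case A: same change in both arms, no intervention effect**

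- d = 0.2, n = 150: 0.2 × 12.247 = 2.449; 2.449 − 1.96 = 0.489; Φ = 0.688.
- d = 0.2, n = 120: 0.2 × 10.954 = 2.191; 2.191 − 1.96 = 0.231; Φ = 0.591.

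Simulation (20,000 runs, t tests) agrees:

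| Common change (SD of change) | Paired test in EG, n = 150 | Paired test in EG, n = 120 | Between-arm test |
|---|---|---|---|
| 0.1 | 23% | 19% | about 5% |
| 0.2 | 68% | 59% | about 5% |
| 0.3 | 95% | 90% | about 5% |

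**Case B: real benefit by slowed decline (EG stable, CG falls 0.4 SD of change)**

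- Paired test in EG: d = 0, so it rejects in 5%.
- Between arms, n = 150: 0.4 × √75 = 3.464; 3.464 − 1.96 = 1.504; Φ = 0.93 (simulation 94%).
- Between arms, n = 120: 0.4 × √60 = 3.098; 3.098 − 1.96 = 1.138; Φ = 0.87 (simulation 87%).

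**Sensitivity to scale.** Express change in baseline SDs, with SD of change √(2(1 − r)) and an assumed baseline to follow-up correlation r of 0.5 to 0.8. A common gain of 0.2 then gives 69% to 97% rejection by the paired test in EG at n = 150, and 59% to 93% at n = 120. If instead EG is stable and CG falls 0.3, the between-arm test has 74% to 98% power at n = 150, and 64% to 96% at n = 120. The paired test in EG stays at 5%.

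**The case against.** The strongest reply is that the plan does give the intervention effect its own method. The sentence on general linear models and repeated measures ANOVA is the only one in the Statistical analysis section that says how intervention effects are assessed, and the Secondary outcomes list also speaks of intervention effects. The paired tests stand next to the baseline comparison, where preliminary tests are often listed. The brackets in the aims may merely name visits. The trial is randomised, and the sample size hypothesis compares the two groups. The exact model term is detail that an article may leave to the full protocol or a SAP, neither of which is shown.

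Much of this stands. A reader might infer that the effect is tested by paired t test alone, or that the plan has a false-positive rate near 68%. The documents support neither. The adjusted models are planned too. No sentence says that a paired p-value decides an aim, or in which arm the paired test is run. The percentages describe a decision rule that the text does not state. The covariate list is also given as examples, so the baseline value is not excluded.

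The reply does not remove what is written. All three aims state a contrast over time, and the analysis section attaches a named test to it. The models that could carry the between-arm comparison could equally be read through their time effect. Nothing ranks the paired tests below the models, so an outcome can have two results that disagree, with no rule for which counts. This is a problem with the stated contrast, not just missing detail.

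**Conclusion.** The point holds in a limited form. For the continuous secondary outcomes, the contrast stated in aims 1 to 3 and the paired t tests cannot answer the question of a randomised trial. The models that could answer it are planned without a named between-arm contrast, without the outcome's baseline value among the listed covariates, and without making the paired tests descriptive.

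The size is conditional. If a paired result in EG were taken as evidence, a common change of 0.1 to 0.3 SD of change would produce a false benefit in 23% to 95% of trials at 150 per arm. A benefit consisting wholly of slowed decline would be found in only 5%. These figures rest on assumed changes and are not error rates of the plan as written. The point does not extend to the binary Corsi outcome, whose sample size hypothesis already compares the groups, or to conversion to dementia. A SAP could settle the matter, but the aims would still need rewording.

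**What to change.** - **Specific aims 1 to 3:** state the comparison as EG versus CG in change from baseline to each of the three follow-ups.
- **Statistical analysis, deciding test:** for each continuous outcome, use the EG minus CG difference at each follow-up, adjusted for that outcome's baseline value, with a 95% CI. Alternatively, use the group-by-visit contrast for that follow-up in the repeated-measures model. State that the time effect is not the test of benefit.
- **Statistical analysis, paired tests:** replace them with within-arm mean changes and CIs, labelled descriptive, and say that significance in one arm but not the other is not evidence of an effect. Describe baseline characteristics by arm without using tests as evidence.

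The cost is wording. The measurements are already planned in both arms, and the models can be run in the same software. The drawback is fewer nominally significant within-arm results to report.

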#### Primary outcome: success of the intervention

The response to the intervention will be evaluated using performance in the Corsi test [25]: an increase of at least 1 point will indicate a success based on the enhancement of the spatial learning processes.

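### Tests are chosen by each variable's observed distribution, without a criterion or a rule for which result decides a non-normal secondary outcome, and the listed covariates omit the outcome's baseline value

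*Protocol article*

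**What the plan says.** All the relevant text is in the Statistical analysis section of the protocol article, which proceeds in this order.

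- Inspection: "A descriptive analysis will be performed to assess the distribution of variables and the presence of possible outliers".
- Normal variables, two comparisons. The first is between arms before treatment: "For normally distributed variables, the comparisons between EG and CG at baseline will be carried out by" a t test or chi-square test. The second is within subjects over time: "while those between baseline and follow-up phases by paired sample" t test.
- Other variables: "For non-normally distributed variables, non-parametric tests will be used". The tests are not named, and no criterion for non-normality is given.
- Treatment effect, with no condition on distribution: "general linear models and repeated measures ANOVA will be used to assess the intervention effects adjusted for confounding variables".
- Covariates, given as examples: "gender, age classes, marital status, schooling, drugs, and other variables that will emerge after analysis of secondary outcomes". The baseline value of the outcome being analysed is not among them.

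The primary outcome is binary. On the Corsi test, "an increase of at least 1 point will indicate a success".

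**The concern.** The continuous secondary outcomes include cognitive, psychological and functional scales, mobility measures, plasma concentrations and the mRNA expression of 84 genes. Several are bounded scores or concentrations, so some skewness is plausible, although the article gives no figures on it.

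For such an outcome the text has two gaps.

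1. **Which result counts.** A variable judged non-normal goes to an unnamed non-parametric test. The same variable may also go to a linear model or repeated measures ANOVA. Nothing says which of the two is the result of the trial for that outcome. The judgement of normality is made on collected data, without a stated criterion, and on the variable itself. What matters for a paired test is the differences, and for a linear model the residuals.
2. **Baseline value.** The outcomes are measured before treatment, yet the outcome's own baseline value is not a listed covariate. It enters at most as one time level of the repeated measures ANOVA.

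At stake are a clear rule for reporting the secondary outcomes, and precision that costs no extra data.

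**Working it through.** The plan has no figure of its own on this point to reproduce. The check asks three questions.

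**Inputs from the article:** 150 per arm (Randomisation) and 20% drop-out (Sample size calculation), so 150 × 0.8 = 120 per arm.

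**Assumed inputs,** because the article gives no SD, skewness or correlation: a 0.3 SD effect; skewness 1 (gamma outcome) or lognormal data with log-SD 0.6; baseline to follow-up correlation ρ of 0.5, 0.6 or 0.7.

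**1. Does choosing the test after a normality check inflate type I error?** Simulation with 150 per arm, ρ = 0.6 and 4,000 runs under no effect, with Shapiro-Wilk standing in for the unnamed check:

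| Route | Skewed (lognormal) | Normal |
|---|---|---|
| Baseline-adjusted model | 4.8% | 5.2% |
| Mann-Whitney at follow-up | 4.8% | 5.2% |
| Check, then choose | 4.8% | 5.4% |
| Either test may count | 8.1% | 8.3% |

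The switch itself does no material harm. The excess to about 8% arises only if two between-arm tests are run and either may be reported.

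**2. Do rank tests lose power?** At 120 per arm, skewness 1 and a 0.3 SD effect, Mann-Whitney on follow-up values has power of about 70–71%, and the unadjusted t test 63–64%. On the same footing the rank test is not the weaker one.

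**3. What does the baseline value add?** With a single follow-up and equal variances, the group-by-time contrast is the comparison of mean changes from baseline. Relative to the unadjusted comparison of follow-up values, the variance is multiplied by:

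- change from baseline: 2(1 − ρ)
- adjusted for baseline: 1 − ρ²

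The ratio of the second to the first is (1 + ρ)/2, which is 0.75, 0.80 and 0.85 at the three correlations. The adjusted model is always at least as precise.

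Approximate power is Φ(0.3 × √(120/2) / √factor − 1.96), where 0.3 × √60 = 2.324:

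| ρ | Factor, adjusted | Power, adjusted | Factor, change | Power, change |
|---|---|---|---|---|
| 0.5 | 0.75 | Φ(2.683 − 1.96) = 77% | 1.00 | Φ(2.324 − 1.96) = 64% |
| 0.6 | 0.64 | Φ(2.905 − 1.96) = 83% | 0.80 | Φ(2.598 − 1.96) = 74% |
| 0.7 | 0.51 | Φ(3.254 − 1.96) = 90% | 0.60 | Φ(3.000 − 1.96) = 85% |

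Simulation with skewness 1 gives 74%, 83% and 89% for the adjusted model, against 64%, 74% and 84% for the group-by-time contrast. This is close to the formula, so skewness of this size does not undo the gain at 120 per arm.

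**The case against.** The strongest case against the point is that the section can be read without conflict. The non-parametric sentence follows the two comparisons for normal variables and most naturally supplies only their alternatives: arms at baseline, and baseline against follow-up within subjects. Intervention effects go to the models whatever the distribution. The article is also a condensed account. The choice of rank test, the normality criterion and any transformations are commonly left to a full protocol or SAP, neither of which is shown. The covariate list is by example, so omission of the baseline value is not exclusion.

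Much of this stands. It rules out three stronger readings that a reader might infer.

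- *Skewed outcomes lose their adjusted treatment effect.* This needs the non-parametric sentence to override the model sentence, and the text does not say that it does. Nor is a baseline-adjusted estimate stated that could be lost.
- *Each skewed outcome carries two competing tests.* Baseline balance, change within subjects and the difference between arms are different hypotheses. The error rate of about 8% applies only if a between-arm rank test is added and either result may count, which the article does not say.
- *The switch to rank tests costs power.* A gap between a baseline-adjusted model and Mann-Whitney comes from the baseline adjustment, not from the ranks.

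The article also names no formal normality test and gives no skewness, so it does not support a claim that most scales would be sent to rank tests.

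The objection does not remove the silence on which result decides a non-normal secondary outcome, or the absence of the baseline value from the named covariates.

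**Conclusion.** The point holds in a limited form. The Statistical analysis section chooses tests from the observed distribution without a criterion. It does not say whether the non-parametric tests or the models decide a non-normal continuous secondary outcome, and its listed covariates leave out that outcome's baseline value. The binary primary outcome is untouched.

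This is an inexpensive improvement, not a flaw that threatens validity. The gain in power over the group-by-time contrast is about 10, 9 and 5 percentage points at correlations 0.5, 0.6 and 0.7 (74 − 64, 83 − 74, 89 − 84). That size rests on the assumed 0.3 SD effect, skewness 1, 120 per arm and a single follow-up. The direction does not depend on the correlation, since (1 + ρ)/2 is below 1 for any ρ below 1.

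**What to change.** State that the between-arm effect on every continuous secondary outcome, whatever its distribution, is estimated by one pre-specified linear model. The model regresses the follow-up value on arm and the baseline value of that outcome, and the arm effect is reported with a confidence interval. Any log transform, for example for plasma concentrations or mRNA expression, should be named before the data are seen. Rank tests become a sensitivity analysis only. Robust standard errors are an option for bounded or skewed scales.

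The cost is a sentence or two and no new data. The small downside is that skewed outcomes are then reported as mean differences, or as geometric-mean ratios after a pre-named log transform, and not as rank tests. If the full protocol or an SAP already fixes this, a reference to it is enough.

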**Methods:**

The prospective randomised controlled trial will enrol 300 subjects with MCI (age ≥ 60 years). Participants will be randomly assigned to: (a) the experimental group, which will undergo sessions of adapted tango, music therapy, engagement in social activities, cognitive intervention and psycho-education for 6 months or (b) the control group, which will receive psycho-education and advice on healthy lifestyle for 6 months. All outcomes will be analysed before intervention (baseline), immediately after termination (follow-up 1), after 6 months (follow-up 2) and after 2 years (follow-up 3).

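### The primary outcome is a binary success powered by logistic regression, but the analysis section uses continuous-outcome models and names no between-arm test of success at follow-up

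*Protocol article*

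**What the plan says.** All references are to the protocol article.

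- **Primary outcome: success of the intervention.** On the Corsi test, "an increase of at least 1 point will indicate a success based on the enhancement of the spatial learning processes". This is a binary responder outcome. No assessment time is attached to it.
- **Sample size calculation.** The null hypothesis is that the "proportion of “success” and “failure” of the intervention is equal in the two groups". The effect is an odds ratio: "Considering an OR = 1.5 indicative of an effect of the intervention". The test is specified as "using logistic regression at the 5% level (two tailed"). The same section describes the outcome this way: "Success and failure were defined on the basis of significant variation in the primary outcomes".
- **Statistical analysis.** Student t and chi-square tests between the arms are tied to baseline. The comparisons over time, "those between baseline and follow-up phases by paired sample" t test, are within-person. For efficacy, "general linear models and repeated measures ANOVA will be used to assess the intervention effects adjusted for confounding variables". Logistic regression does not appear.
- **Abstract, Methods.** "All outcomes will be analysed before intervention (baseline), immediately after termination (follow-up 1), after 6 months (follow-up 2) and after 2 years (follow-up 3"). Specific aim 1, which covers cognitive performance, likewise sets baseline against each of the three follow-ups without ranking them.

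**The concern.** The sample size section and the analysis section describe two different analyses of the trial's main question. One compares proportions of responders and gives an odds ratio. The other compares mean scores or mean changes. They need not agree: a shift in the mean Corsi score can occur with little change in the share who gain a point, and the reverse is also possible. A power statement for one does not carry over to the other.

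Two further gaps add to this. Success is described once as significant variation in several outcomes and once as a fixed gain on one test. The primary test also has no named follow-up. The definition, the model and the time point of the primary comparison can then still be chosen after results are known, which is what a prespecified primary analysis is meant to prevent.

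**Working it through.** **1. The article's own figure.** Stated: 90% power, 300 subjects (150 per arm), OR 1.5, two-sided 5%, logistic regression. The control success rate is not given, so it is varied here as an assumption.

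For control rate p, the experimental rate is q = 1.5p/(1 − p + 1.5p). With n per arm,

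power ≈ Φ( ln 1.5 / √[1/(n·p(1−p)) + 1/(n·q(1−q))] − 1.960 ).

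The most favourable case is p ≈ 0.45, where q = 0.551:

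- n = 150: standard error = √(1/37.13 + 1/37.11) = 0.232. Then 0.405/0.232 = 1.747, and Φ(1.747 − 1.960) = Φ(−0.213) = 41.6%.
- n = 120 (150 less the stated 20% drop-out): standard error = √(1/29.70 + 1/29.69) = 0.260. Then 0.405/0.260 = 1.562, and Φ(−0.398) = about 35%.

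| Control success rate | 0.1 | 0.2 | 0.3 | 0.4 | 0.45 | 0.5 | 0.7 |
|---|---|---|---|---|---|---|---|
| Power, 150 per arm | 20.5% | 31.6% | 38.3% | 41.3% | 41.6% | 41.3% | 33.4% |

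The 90% does not reproduce for a two-arm comparison. A value near it (89.6%, overall success rate 0.3, N = 300) appears if OR 1.5 is taken per standard deviation of a continuous covariate, which is not the hypothesis stated. This is a separate problem. It matters here only because it limits what the fix achieves.

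**2. Each named method against the primary comparison.** The comparison needed is between arms, at follow-up, on a binary success.

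| Method in Statistical analysis | Between arms? | At follow-up? | Binary success? |
|---|---|---|---|
| t or chi-square test | yes | no, baseline only | chi-square could be |
| Paired t test | no | yes | no |
| Non-parametric substitutes | as the tests they replace | as the tests they replace | none named |
| General linear models, repeated measures ANOVA | yes | yes | no, continuous-outcome methods |

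No row meets all three requirements. The method that does, logistic regression, is named only under Sample size calculation.

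**3. The two descriptions of success.** Sample size calculation: plural outcomes, significant variation, no threshold. Primary outcome section: one test, 1 point. Only the second can be coded as success or failure for each participant.

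**4. Three follow-ups.** If each were tested at 5% and any one sufficed, family-wise error would be 1 − 0.95³ = 14.3% under independence. Simulation of three correlated normal statistics gives 12.5% at correlation 0.5 and 10.9% at 0.7. The correlations and the any-of-three rule are assumptions.

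**The case against.** The best defence is that the article is a condensed account. The sample size section already gives the null hypothesis, test, level and sidedness, and the analysis section omits that test without excluding it. A full protocol or SAP could supply the model and the time point. This has force for the missing follow-up designation, which alone would be ordinary omitted detail, and for a model for conversion to dementia, which is not pressed here. It does not dispose of the main point, because the analysis section is not silent: it says which models assess intervention effects, and they are not the one powered.

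It is also true that linear models and ANOVA can compare arms at follow-up, and that repeated measures ANOVA can take the visits in one model. But they do so on a continuous score. A linear model could be fitted to a 0/1 indicator, but it would estimate a difference in proportions and not the odds ratio, and the article does not propose it. If generalised linear models were meant, the text needs correcting.

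On the definition, the phrase in the sample size section may be a loose general statement that the 1-point rule makes precise. That is a fair reading, so this part is an alignment of wording and not a second endpoint.

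A reader might also infer that efficacy will be claimed when the paired test is significant in the experimental arm and not in the control arm. The documents do not support this, since they give intervention effects to the linear models and ANOVA. Nor can the risk be sized firmly. With no arm difference, 120 per arm and an equal practice gain in both, that pattern has probability P(1 − P), where P is the power of one paired test. This cannot exceed 25%. It is about 7%, 15%, 24%, 9% and 1% for gains of 0.05, 0.1, 0.2, 0.3 and 0.4 SD. The gain is unknown, so about 1% to 24% is all that can be said, and it concerns a continuous score and not the binary success.

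**Conclusion.** The point holds as a conflict within the article. The primary outcome is binary and is powered for a between-arm logistic regression, while the stated models for intervention effects are continuous-outcome methods and no between-arm test of the success proportion at follow-up is named. This conclusion comes from the text and rests on no numerical assumption. It needs correction because it concerns the primary inference.

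The looser description of success and the undesignated follow-up make it worse but are lesser points. The 11–14% family-wise error is conditional on a decision rule that a reader might infer from three unranked follow-ups. The article gives an assessment schedule and states no such rule. It also cannot be said that the powered test will not be run, only that the analysis section does not provide for it.

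**What to change.** In Statistical analysis, state one primary analysis: logistic regression of success (Corsi gain from baseline of 1 point or more) on randomised arm, adjusted for baseline Corsi, two-sided 5%, at one pre-named follow-up. Follow-up 1, at the end of the intervention, is a reasonable proposal, but the article does not rank the follow-ups, so the investigators must choose. Make the other follow-ups secondary. Keep general linear models and repeated measures ANOVA for continuous outcomes, and label paired within-arm tests descriptive. In Sample size calculation, replace the reference to significant variation in the primary outcomes with the 1-point definition.

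The cost of these edits is wording in two sections and one decision on timing, to be fixed before follow-up Corsi results are compared by arm. No new data are needed. Naming logistic regression does not deliver the stated 90% power, however. The sample size section needs its own restatement, with the assumed control success rate given, because at OR 1.5 the power is at most about 42% with 150 per arm and 35% with 120.
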